### Study design

The trial is designed as an unblinded, RCT to assess the efficacy of a complex behavioural change intervention aiming to improve the overall health of young women prior to their first pregnancy. The intervention follow-up period is 8 months from randomisation/baseline. After end trial the subjects will be monitored for a period of 12 months for pregnancy. Figure 1 gives the flow diagram of the trial. The trial was designed following the Standard Protocol Items: Recommendations for Interventional Trials (SPIRIT) 2013 statement (see Additional file 1).

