#### Other endpoints

The incidence of GDM, confirmed by an oral glucose tolerance test (OGTT), will be assessed in the subjects who will complete the intervention period and who become pregnant in the post-trial monitoring period. The OGTT will be taken at weeks 26–28 of the pregnancy. Data will be captured retrospectively and obtained from medical charts.

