#### Sample size calculation

The sample size calculation is based on a 2-cm reduction in waist circumference, in the primary endpoint of waist circumference between the intervention and control arms at 8 months. Assuming a 5 % level of significance (alpha = 0.05), a statistical power of 90 % (beta = 0.10) and a SD of 5 cm using a two-sided *t* test, 132 women per arm are required. Taking into consideration a 20 % drop-out rate, and that 20 % will be pregnant, a total of 660 women would be randomised/enrolled to ensure 264 subjects to cover both the intervention and control arms.

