**Table 2 Tab2:**
[figure not shown]
Data collection at each time-point in the Jom Mama trial

Data collection on woman;● Data collection on spouse; ^a^
*FFQ* Food Frequency Questionnaire, ^b^
*IPAQ* International Physical Activity Questionnaire, ^c^
*DASS*-*21* Depression Anxiety and Stress Scale 21-items, ^d^ Fasting lipid profile: will be measured as a combination of: total cholesterol (TC) level, low-density lipoprotein cholesterol (LDL-C) level, high-density lipoprotein cholesterol (HDL-C) level and triglyceride (TG) level; 
^5^Exit point visit will occur if the woman becomes pregnant between 4.1 months and 8 months after randomisation

If a subject becomes pregnant within the 8-month intervention period, she will be withdrawn from the trial. Exit measurements, which are similar to those at the endpoint visit, will be performed only for subjects who become pregnant between 4.1 and 8 months from baseline. For those who become pregnant between baseline and month 4 in the intervention period, no measurements will be taken.

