#### Statistical analysis

The null hypothesis is that there is no difference in the change in waist circumference between the intervention and the control group after the 8-month intervention. The alternative hypothesis is that the decrement in waist circumference will be bigger in the intervention group compared to the control group after the 8-month intervention. A linear regression model will be used to assess the difference in the change of waist circumference from baseline to end of intervention, with the difference in waist circumference as the independent variable, treatment (intervention versus control) and baseline waist circumference as covariates. Additional tests will be performed for the impact of the intervention in both high- (waist circumference above 80 cm) and low-risk (waist circumference below 80 cm) groups. This will be done by subgroup analysis or by assessing the proportional changes in the primary endpoint. Each subgroup will also be analysed in a linear regression model. The continuous secondary endpoints will be analysed in a linear regression model, whereas the difference in the change of each secondary endpoint from baseline to end of intervention, will be the dependent variable, treatment (intervention versus control) and baseline value as covariate. Regarding health literacy (HL-EU-Q47), physical activity (IPAQ) and stress (DASS-21) all the variables are ordinal and, therefore, independence between intervention and control groups will be tested with the chi-squared test. Change in nutrient intakes will be compared between the groups using a generalised linear model, with additional adjustments for total energy intake. Nutrient and food patterns before and after the intervention will be explored in both groups separately by using dimension reduction techniques such as principal component analysis. Multivariate analysis will be performed to assess the association between exposure to the intervention, primary endpoints and secondary endpoints (BMI, waist-to-height and waist-to-hip ratio, HbA_1c_, lipid profile, blood pressure, health literacy, physical activity, dietary intake and stress level) using linear regressions. In this model the secondary endpoint will be included in the model as covariates and the estimated coefficients will be presented unadjusted and adjusted for appropriate and/or effect modifier and/or confounders. Furthermore, interactions between the secondary endpoints will also be explored. Several supportive analyses will be performed. The first supportive analysis will explore the relation between subjects’ and spouses’ change in waist circumference and other anthropometric measurements, diet, physical activity, health literacy and stress. A second supportive analysis will explore whether a short intervention period (subjects who become pregnant between 4.1 and 8 months in the intervention period), will also have an impact on the primary endpoint and secondary endpoints. A time variable explaining how long they have been included in the intervention will be included in the models as a covariate. At the end of the 12-month post-intervention monitoring period, a full analysis will be conducted on subjects who become pregnant within 12 months after completing the intervention. This will be done by assessing the incidences of GDM among women who became pregnant between treatment groups, using a chi-squared test. Additionally, a logistic regression model to explore associations between the number of subjects with GDM and several secondary endpoints will be conducted.

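### The gestational diabetes analysis is set for the end of the same 12 months in which pregnancies are counted, so women who conceive late in that window have no glucose-test result when it is run

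*Protocol article*

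**What the plan says.** Three sections of the protocol article bear on the timing.

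- **Study design** sets the monitoring period: "After end trial the subjects will be monitored for a period of 12 months for pregnancy".
- **Other endpoints** defines the outcome and how it is obtained. GDM must be confirmed by OGTT, and "The OGTT will be taken at weeks 26–28 of the pregnancy". It is assessed "in the subjects who will complete the intervention period and who become pregnant in the post-trial monitoring period". On the source: "Data will be captured retrospectively and obtained from medical charts".
- **Statistical analysis** fixes both date and population: "At the end of the 12-month post-intervention monitoring period, a full analysis will be conducted on subjects who become pregnant within 12 months". Those months are counted from the end of the intervention. The arms are compared on GDM incidence among the pregnant women by a chi-squared test, and a logistic model for GDM is added.

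Two further statements define who is left out and how often that is expected. In the text after Table 2: "If a subject becomes pregnant within the 8-month intervention period, she will be withdrawn from the trial". The Sample size calculation allows for a 20 % drop-out and assumes "that 20 % will be pregnant".

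No section gives a period between the last day on which a conception counts and the day on which GDM data are taken from the charts.

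**The concern.** A woman enters the GDM population on the day she conceives, but her outcome does not exist until about half a year later. If the analysis is run when the conception window closes, every woman who conceived in roughly its second half belongs to the denominator and has no result.

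The plan does not say what happens to her. If she is dropped, the comparison loses pregnancies from an outcome that already has few. If she were counted as pregnant without GDM, incidence would be understated in both arms. GDM is listed among the other endpoints and carries no power claim. It is, however, the trial's only planned look at the pregnancy course that motivates the project in the Background, and avoidable loss there is worth preventing.

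**Working it through.** **Plan's own figures.** The article gives no event count or power for GDM. The figure it does give reproduces: with a difference of 2 cm, SD 5, two-sided alpha 0.05 and power 90 %, n per arm = 2 × (1.960 + 1.282)² × 5² / 2² = 131.4, rounded up to 132, or 264 in all.

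**Inputs from the article.** Monitoring of 12 months; OGTT at weeks 26–28; 20 % pregnant, taken here to refer to the 8-month intervention; 264 completers.

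**Assumptions.** Constant conception hazard. Weeks dated either from the last menstrual period (conception at week 2) or from conception, because the article does not say which. 4.348 weeks per month.

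**Step 1: lag L from conception to test.**

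- Week 26 from last period: 24 / 4.348 = 5.52 months
- Week 28 from last period, or week 26 from conception: 26 / 4.348 = 5.98 months
- Week 28 from conception: 28 / 4.348 = 6.44 months

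The last conception month with a result at month 12 is 12 − L = 6.48, 6.02 or 5.56.

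**Step 2: conception rate.** Hazard h = −ln(0.8)/8 = 0.0279 per month (2.75 % per month). With F(t) = 1 − exp(−ht), F(12) = 0.284.

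**Step 3: each woman cut at her own month 12.** Untested share = 1 − F(12 − L)/F(12).

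| L (months) | F(12 − L) | Untested, constant hazard | Untested, uniform conception (L/12) |
|---|---|---|---|
| 5.52 | 0.165 | 42 % | 46 % |
| 5.98 | 0.155 | 46 % | 50 % |
| 6.44 | 0.144 | 49.5 % | 54 % |

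At assumed higher conception rates of 5–15 % per month, the range is 24–46 %. With 264 completers, about 264 × 0.284 = 75 conceive in the window, of whom 31–37 are untested.

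**Step 4: one cut at the last woman's month 12.** A woman enrolled u months before the last one gains u months, so she is tested if she conceives by month 12 − L + u. With enrolment uniform over R months (assumed) and m the smaller of R and L:

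Untested share = A / (R × F(12)), where A = [exp(−h(12 − L)) − exp(−h(12 − L + m))]/h − m × exp(−12h).

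| L (months) | A | R = 6 | R = 12 | R = 18 |
|---|---|---|---|---|
| 5.52 | 0.320 | 19 % | 9 % | 6 % |
| 5.98 | 0.377 | 22 % | 11 % | 7 % |
| 6.44 | 0.44 | 26 % | 13 % | 9 % |

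**Step 5: when the data are complete.** The last woman to conceive at month 12 reaches week 28 at 12 + 5.98 = 18.0 months after the endpoint visit (18.4 if weeks run from conception).

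**Step 6: calendar.** Trial status gives a November 2015 start and completion by July 2017, which is 20 months. That equals 8 + 12 months for the first woman enrolled. If completion includes monitoring, there is no room even for her test. If it means the intervention phase only, 20 − 8 = 12 months of recruitment are implied, the middle column of Step 4.

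**The case against.** **A single analysis date.** The article describes one analysis, which reads naturally as a trial-level event after the last woman's month 12. The Discussion also expects recruitment to run longer than first planned. Women enrolled early would then have passed their test wherever in the window they conceived. This stands, and it is why a loss of nearly half cannot be presented as the plain result. It does not remove the problem, because late-enrolled women who conceive late remain untested.

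**Retrospective chart capture.** GDM data come from charts after the event, so the look-up could be made later, and the full protocol may say so. That is possible. But the article does more than leave the date open: it fixes the analysis at the end of monitoring, which conflicts with its own test timing.

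**Understated incidence.** A reader might infer that untested women will be counted as free of GDM. No section says this, and the endpoint definition requires an OGTT. If they are left out, the same calendar rule applies to both arms and the main cost is precision.

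**Pregnancies during the intervention.** A reader might also infer that leaving these out is an error that discards more pregnancies than it keeps. Taking 20 % of 660 gives 132 excluded, against about 75 post-trial pregnancies on 264 completers, or about 113 if 60 % of 660 (396) complete. But the restriction is an openly stated design choice and is consistent across sections. Women who conceive early have had little of the intervention, and the article does not show whether charts may be consulted after withdrawal. Statisticians can reasonably differ here. What remains is that the comparison conditions on completing the intervention and then conceiving, both of which follow randomisation.

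**Conclusion.** The timing conflict is real. Study design, Other endpoints and Statistical analysis cannot all be followed for a woman who conceives after about month 5.6–6.5 of monitoring.

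Its size depends on a reading that the article leaves open: about 42–50 % of in-window pregnancies untested under individual month-12 cuts, and about 6–22 % (up to 26 % on the longest lag) under a single cut with 6–18 months of uniform recruitment. Both ranges rest on a constant hazard derived from the 20 % figure. Recruitment length and enrolment pattern are assumptions. The hazard is uncertain too, since engaged women not yet married are eligible.

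The documents support neither a claim that GDM incidence will be understated nor a claim that the completer restriction is a mistake. The restriction does mean that the chi-squared result is not a comparison of the groups as randomised. The primary endpoint is untouched.

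**What to change.** Keep the 12-month conception window and separate it from the analysis date. State that charts will be extracted and GDM analysed only once the last woman conceiving in the window has passed week 28, about 18 months after the last endpoint visit.

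If that delay is not acceptable, limit the denominator to pregnancies that have reached the OGTT week by the extraction date. Define this by gestational dating rather than by whether a result happens to be on file, and report how many in-window pregnancies are thereby left out of each arm.

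In either case, say how in-window pregnancies without an OGTT result are handled, and describe the comparison as non-randomised because it conditions on completing the intervention and then conceiving. Adding women who conceive during the intervention is an optional sensitivity analysis, if chart access after withdrawal permits.

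The first option costs about 6 months' delay to this endpoint only. The second costs no time but loses pregnancies. Neither changes a visit, a measurement or the primary analysis.

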
#### Ethical, regulatory and data management considerations

The study protocol version 4.0 dated 12 August 2015 has received ethical and governance approvals by the Medical Research and Ethics Committee of the Ministry of Health Malaysia (protocol number: NMRR-14-904-21963) on 21 September 2015. The study is performed in compliance with the Declaration of Helsinki. Written informed consent will be taken from each participant prior to study enrolment by trained study nurse. The trial was registered at ClinicalTrials.gov, Identifier: NCT02617693 on 30 November 2015.

#### Safety monitoring

In the event of an abnormal laboratory test results for Hb1Ac or a newly suspected or diagnosed health concern during a subject’s measurements (i.e. high blood pressure or a high score in the DASS-21 tool) at baseline/exit point/endpoint, the subject will be referred to their primary health care physician for further examination.

## Discussion

This study protocol describes the first community-based RCT to examine the efficacy of a complex behavioural change lifestyle intervention in improving the pre-pregnancy health of young Malaysian couples. Other studies assessing the prevention of GDM and T2DM have mainly focused on high-risk groups or the intervention entry point has been in the first trimester of the women’s pregnancy [36–40], whereas few RCT studies exist on low-risk populations or on an intervention entry point in the pre-conception period [41]. To develop population strategies, instead of targeting high-risk groups it is imperative to widen the focus to the general population, especially in a country such as Malaysia where the prevalence of diabetes and obesity has increased alarmingly in the last 10 years [2]. One European study has shown that limited guidelines and policies exist in this area, as guidelines and policies are designed to mainly target high-risk groups [42]. Therefore, this study may contribute evidence to this important area which is needed to support policy-makers in making rational decisions to improve population health.

A pilot test was conducted prior to trial implementation and has identified a number of challenges. A major challenge that has been found is that the intervention addresses a challenging period for young Malaysian couples, whereby busy work schedules and lack of time affect participation rates and generate low interest in such an intervention. While it would be ideal to collect spousal data at baseline and endpoint, it will be made optional for the spouse to attend both baseline and endpoint visits if they are unable to attend in order to continue with recruitment. Based on these observations, it is expected that the recruitment period will be longer than initially anticipated.

The combination of motivational interviewing through a CHP and E-health platform is a novel approach. Training the community nurses to become CHPs involves an interactive approach beyond their conventional training programmes; this provided new learning experiences for these nurses to build higher capacity in patient engagement. The E-health platform is also a new experience for the primary health care services in the Seremban district and considerable time was needed to train community nurses with the necessary IT skills. Another key challenge faced was the limited usage of the E-health mobile application due to poor Internet connectivity in the district of Seremban. In mitigating this challenge, Wi-Fi hotspots in the designated primary health clinics have been set up to enable participating women and their spouses to download the mobile application in a secured Internet environment. Additionally, several changes have been made to the E-health platform to make it more robust.

The proposed trial will not directly assess the long-term effects of the intervention on the risk of the offspring developing T2DM. Given the complexity of developing, implementing and evaluating complex behavioural change lifestyle interventions, this trial will focus on improving the pre-conception health in young women prior to their first pregnancy.

## Trial status

The trial started recruitment in November 2015. The trial is expected to be completed by July 2017.

## Abbreviations

BMI: body mass index
CHP: community health promoter
DASS-21: Depression Anxiety and Stress Scale 21-items
DBP: diastolic blood pressure
DM: diabetes mellitus
DOHaD: The Development Origins of Health and Disease
FFQ: Food Frequency Questionnaire
GDM: gestational diabetes mellitus
HbA_1c_: glycated haemoglobin A_1c_
HDL-C: high-density lipoprotein cholesterol
HLC-EU-Q47: The European Health literacy Survey Questionnaire
ID: identification
IHSR: Institute for Health System Research
IPAQ: International Physical Activity Questionnaire
LDL-C: low-density lipoprotein cholesterol
MoH: Ministry of Health
NCDs: non-communicable diseases
NHMS: National Health and Morbidity Survey
OGTT: oral glucose tolerance test
RCT: randomised controlled trial
SBP: systolic blood pressure
SD: standard deviation
T2DM: type 2 diabetes mellitus
TC: total cholesterol
TG: triglycerides
WHO: World Health Organisation
